## 8.3 Outcome Procedures

### 8.3.1 Pure tone audiogram

Pure tone audiometry will be undertaken in clinics by audiologists blind to treatment allocation, in accordance with the British Society of Audiology Recommended Procedure for pure-tone air-conduction and bone conduction threshold audiometry with and without masking (2018) (25).

### 8.3.2 AB word speech testing

Audiologists blind to treatment allocation will perform speech testing, using AB wordlists on each ear individually. Supra-aural headphones (TDH-39) are routinely used, but insert earphones may be selected at the audiologist's discretion, taking care to select the appropriate routing and masking levels.

The ear with the best audiometric thresholds will be tested first to allow the participant to become familiarised with the task. The initial presentation level (Decibel Sensation Level, above PTA) will be around 30-40 dB above the PTA average across 250, 500 and 1000Hz. Masking of the contralateral ear will be applied in order to prevent the non-test ear being able to hear the speech material presented to the test ear. If the participant has a sensorineural hearing loss the masking noise will be presented 30 dB below the speech signal. The appropriate level of masking noise for sensorineural, conductive and mixed losses is derived from the following equation (26):

$$Ds + Em + \max ABG_{nt} - 40$$

Where:

- Ds is the dial setting for presentation of speech to the test ear
- Em is effective masking calculated by measuring the difference in dial setting for speech presented to normal listeners at a level giving over 95% in quiet and the dial setting of noise presented to the same ear which leads to speech scores less than 10%. This factor has previously been measured and found to be 10 dB using a local biological calibration
- Max ABGnt is the maximum air-bone gap in the non-test ear 250 to 4000 Hz
- '40' comes from minimum interaural attenuation for masking in audiometry using headphones (note for inserts this would be 55 dB).

Each word is scored as a maximum of 3, one point for each correct phoneme. For the purpose of the study, the aim is to establish the Maximum Recognition Score (MRS), also known as PBmax for a phonemically balanced word list. Following completion of the first list, the presentation level should be increased in 10dB steps above the initial presentation level until one of the following:

- 3 points are obtained with scores over 95%
- Roll-over is clearly identified (a decrease in score at a minimum of two levels beyond the MRS)
- The maximum output of the audiometer is reached
- The participant reports discomfort

---

### 8.3.3 Assessor training

Training will be provided for audiologists not familiar with AB word testing. This will be recorded on a training log which should be kept in the ISF. This will take the form of written material and a short video on the testing technique. For any audiologists seeking additional help, remote one to one training will be provided via videoconferencing software. The AB word training material will be available at: <https://entintegrate.co.uk/issnhl-rct>

### 8.3.4 Online hearing tests

Bespoke software has been developed for the trial by the HearX Group to allow regular interval testing to chart the recovery of hearing. This will be hosted on the trial website, and will allow participants to self-test their hearing online at home. It will be recommended that participants complete the online tests weekly for the 12 week follow up period, however this part of the trial will be optional. Participants without internet access or the required skills, or those who prefer not to test at home will still be able to participate in the trial.

On visiting the website participants will be asked to enter their unique identifier provided at randomisation, and to connect headphones to the computer or device they are using. Headphones will be provided if participants do not have access to their own.

First participants will complete a digits in noise test that has been widely used in a World Health Organisation hearing screening app (34). The trial version will be modified to allow the collection of ear-specific data. Data from both ears will be collected, with the contralateral ear providing a measure of test-retest variability. Next participants will complete pure tone audiometry, again collecting ear-specific thresholds.

Participants will finish the online testing by marking the severity of their dizziness and the severity of their tinnitus on a 0-10 visual analogue scale (VAS) using a slider.

It will be recommended that participants use the same location and approximate time for the hearing tests, in an attempt to improve the consistency of results and to aid in regular testing. HearX has significant experience with digital remote hearing assessment, however additional validation procedures have been included in the study analysis plan to assess if online thresholds accurately reflect in-hospital hearing test results. Online hearing tests conducted within a few days of the pre-injection pure tone audiogram tests, or the 6 and 12 week pure tone and speech tests, will be compared to the audiologist performed hearing tests.

## 9 TRIAL PROCEDURES

### Baseline

The following should be performed and/or collected:

- Informed consent
- Medical history
- Concomitant medication check
- Demographic information
- Pure tone audiogram (0.5-8.0kHz range) - should be performed within 3 days prior to commencement of treatment
- AB phoneme speech testing- recommended to be performed on same day as pure tone audiogram or if not practicable within next working day
- Participant completed questionnaires to include SSQ, VRBQ, TFI, HUI3, ICECAP-A
- Oral steroid arm and combination treatment arm- prescribe oral steroids

- 
- Intratympanic injection arm and combination treatment arm - 1st intratympanic injection (for the combination arm, injection should be given within a period  $\pm 4$  days of starting oral steroids).

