### 1.2.2 Justification for design

STARFISH is a three arm, superiority randomised, controlled trial. The three arms reflect the variation in current practice and the trial aims to elucidate which of these three arms is the optimal (superior) treatment. Randomised controlled trials are considered “gold standard” for evidence-based medicine.

Procedurally, the trial is designed to be in line with standard clinical practice as much as possible, to minimise burden on participants. The four week recruitment window from symptom onset reflects current practice, where more than half of UK surgeons would use intratympanic steroids up to one month after onset (9). Two meta-analyses suggest that the final hearing threshold may be independent of the delay in steroid treatment, for both primary (10) and secondary therapy (11), supporting the four-week treatment window, which is longer than some other trials adopt.

PPI suggested concern over recovery of hearing outweighs the anxiety associated with more invasive intratympanic steroid treatment, with randomisation acceptable to 80% of those surveyed. Reasons for the chosen minimisation variables include: there is a correlation between the hearing threshold before treatment and recovery (10); progressive spontaneous recovery may mean those treated later have already undergone some recovery; vertigo is a poor prognostic indicator (33).

---

Patient and public involvement in trial design led to the adoption of many of the outcome measures, including speech, tinnitus and dizziness questionnaires, and the optional participant-led home testing. The use of a modified classification system for recovery was suggested by participants, allowing the audiogram data to be translated into more relevant and meaningful measures to participants.

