#### **5.1 Consent Procedure**

Participants with confirmed ISSNHL will be approached about the trial by their clinical care team during the standard clinical appointment following referral to secondary care.

A Participant Information Sheet (PIS) will be provided to facilitate this process, which may be presented electronically. Participants will also be invited to watch a short explanatory video on their own smartphone, tablet or hospital computer at <https://entintegrate.co.uk/starfish>. The PI or delegate will ensure that they adequately explain the aim of the trial, trial interventions, and the anticipated benefits and potential hazards of taking part in the trial to the participant. They will also explain that participation is voluntary and that the participant is free to decide to take part and may withdraw from the trial at any time without affecting their care.

---

The participant will be given sufficient time to read the PIS and discuss their participation with others outside of the clinical or research team. The participant will be given the opportunity to ask questions before electronically signing and dating the latest version of the Informed Consent Form (ICF). Paper copies of the PIS and ICF will also be available from the Trial Office and will be printed or photocopied onto the headed paper of the local NHS Trust.

**Given the urgent need to commence treatment for the condition, randomisation and commencement of treatment should ideally occur on the same or next working day after written consent has been gained.**

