### **6.3 Screening and enrolment**

An ENT clinician will confirm the diagnosis of ISSNHL via a pure tone audiogram. The potential participant will be asked by the clinical team if they are willing to speak to a member of the site research team to find out about the trial in more detail and to perform a complete eligibility assessment.

A medically qualified doctor who is delegated the task on the **STARFISH Site Signature and Delegation Log** will confirm eligibility. Investigators should consider the participant's medical history when determining if the sudden sensorineural loss is idiopathic. Pre-existing conditions such as ipsilateral Meniere's disease or multiple sclerosis that represent a high chance of being the aetiology for the hearing loss would make the participant ineligible for enrolment.

If the participants meet all the eligibility criteria and confirm that they are willing to take part in the trial, they will be asked to formally consent to participate in the trial as described in section 5.

Details of all participants approached about the trial will be recorded electronically on the **STARFISH Participant Screening/Enrolment Log**, which is part of the trial system. Since screening will occur prior to the participants providing consent, they will be identified by their sex, year of birth and date of screening only on the screening log.

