## 8.2 Main Trial Outcomes

### 8.2.1 Primary Outcome

- **The absolute improvement in pure tone audiogram average at 12 weeks** following randomisation (calculated at 0.5, 1.0, 2.0, 4.0 kHz). Conducted by an audiologist blinded to the treatment allocation.

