| Resource usage                                         |           |          |                                               |                                               |                    | All               | All                  |
| Adverse Events monitoring                              |           |          |                                               |                                               |                    | All               | 2,3 & |
| Compliance reporting                                   |           |          |                                               |                                               |                    | All               |                      |
| Oral steroid provision                                 |           | 1,3      |                                               |                                               |                    |                   |                      |
| Intratympanic injection                                |           | 2,3      | 2,3                                           | 2,3                                           |                    |                   |                      |

---

1 = for arm 1 (oral steroid), 2 = for arm 2 (intratympanic injection), 3 = for arm 3 (combined treatment)

#Optional, for participants who have internet access.

\* should be performed within three days prior to commencement of treatment

\*\*recommended to be performed on same day as pure tone audiogram or if not practicable within next working day

& Only persistent perforation of the tympanic membrane will be recorded at 12 weeks

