## 11.2 Case Report Form Completion

CRFs should be completed for each individual participant.

The CRFs will include, but not be limited to, the forms listed in Table 9.

**Table 9:** List of trial specific CRFs

| Form Name                    | Schedule for submission                                                                                                                                                      |
|------------------------------|------------------------------------------------------------------------------------------------------------------------------------------------------------------------------|
| Screening log                | When a patient presents with ISSNHL and is considered for approach to participate in the STARFISH trial                                                                      |
| Contact details form         | Following consent                                                                                                                                                            |
| Randomisation CRF            | At the point of randomisation                                                                                                                                                |
| Clinic visit form            | At baseline (i.e. following consent and randomisation);
At 2nd injection visit (if applicable);
At 3rd injection visit (if applicable);
At 6 weeks;
At 12 weeks. |
| Participant-complete booklet | At baseline (i.e. following consent and randomisation);
At 6 weeks;
At 12 weeks.                                                                                       |

|                                  |                                                                        |
|----------------------------------|------------------------------------------------------------------------|
| Serious Adverse Event Form       | In accordance with section 10                                          |
| Trial Exit/Change of status Form | At the point of becoming aware of withdrawal/change of status or death |

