### 14.2.1 Primary outcome

The primary outcome is the absolute improvement in pure tone audiogram average at 12-week following randomisation (calculated at 0.5, 1.0, 2.0, 4.0 kHz). This data is collected at

---

baseline and at each follow-up visit. The data for this outcome is continuous and therefore will be summarised using the mean and standard deviation along with minimum and maximum values with respect to the intervention arms and overall at each time-point.

Difference between group means and associated 97.5% confidence intervals at each time-point will be estimated through the use of a repeated measures mixed-effects linear regression model. All assessment times (baseline and the post-treatment time points) will be included. Parameters allowing for participant, treatment group, time variable, the randomisation minimisation variables and the baseline score will be included (all as fixed effects). Time will be assumed to be a categorical (fixed) variable. To allow for a varying treatment effect over time, a time by treatment interaction parameter will be included in the model. Estimates of differences between groups at the 6 week and 12 week time-point will be taken from the model including this interaction parameter. Results will be presented as adjusted mean difference and 97.5% confidence interval. Longitudinal plots of the data over time will be constructed for visual presentation of the data.

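### The primary-outcome baseline audiogram is timed from treatment start, not randomisation, so the starting value could come to depend on arm if treatment delays differ

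*Protocol*

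**What the plan says.** Section 8.2.1 defines the outcome as "The absolute improvement in pure tone audiogram average at 12 weeks" after randomisation, and section 14.2.1 repeats it: "The primary outcome is the absolute improvement in pure tone audiogram average at 12-week following randomisation". The 6- and 12-week visits are also counted from randomisation.

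The starting value uses a different clock. Section 9 (Baseline) says the audiogram "should be performed within 3 days prior to commencement of treatment", and the footnote to Table 3 says the same for all arms: "should be performed within three days prior to commencement of treatment".

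An audiogram before randomisation always exists. Section 6.3 states: "An ENT clinician will confirm the diagnosis of ISSNHL via a pure tone audiogram". Section 6.4.3 also needs the pure tone average for the minimisation severity stratum. No section says that this audiogram is the baseline for the primary outcome.

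On delay, section 5.1 says that "randomisation and commencement of treatment should ideally occur on the same or next working day" after consent. This is an aim with no upper limit. Section 7.11.1 limits treatment start to 4 weeks from symptom onset, for per-protocol status only.

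**The concern.** A change outcome in a randomised trial should start from a value fixed before allocation. Here the reference point is treatment start, which comes after allocation and can depend on the allocated arm.

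The protocol gives reasons to care about a few days. Section 1.1 cites spontaneous recovery in 32-65% of cases, and section 1.2.2 says that "progressive spontaneous recovery may mean those treated later have already undergone some recovery". Suppose one arm's baseline is re-measured later than another's. Recovery in the interval then counts as gain in the arm measured early and disappears from the arm measured late. At stake is one of the two key comparisons, intratympanic versus oral.

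A longer lag to injection than to tablets is plausible. Tablets are only prescribed. An injection needs a microscope or endoscope, topical anaesthesia, 30 minutes lying down (section 7.3) and a clinician who has reviewed the training material (section 7.4). In the combined arm the protocol itself accepts up to four days between tablets and first injection, one day more than the audiogram window. In that arm the earlier treatment anchors the baseline. In the intratympanic-only arm the injection is the only anchor.

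**Working it through.** **Step 1: the plan's own figure.** Inputs from section 14.1: difference 10 dB, SD 25 dB, alpha 0.025 per comparison (two-sided), power 90%. The normal approximation gives 156 per arm. With the t distribution, power is 89.9% at 156 and 90.1% at 157, so the stated 157 is reproduced. 157/0.9 = 174.4, rounded up to 175 per arm, or 525 in total. The sample size is not in question, and the fix leaves it unchanged.

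**Step 2: when the rule calls for a new baseline.**
- Treatment within 3 days of the eligibility audiogram: that audiogram qualifies and nothing is lost. Friday to Monday is exactly 3 days and still qualifies.
- Treatment more than 3 days after it: the audiogram is out of window. Either the rule is broken or a new audiogram is taken, possibly after randomisation.
- Between-arm bias arises only if the second case is more frequent in one arm **and** the repeat is used as baseline.

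**Step 3: effect on the estimate.** Let the mean baseline in one arm be lowered by

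shift = share of the arm repeated × days of delay × recovery per day.

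An unadjusted change score is biased by the full shift. With baseline as a covariate (section 14.2.1) the bias is slope × shift, where the slope is that of the 12-week threshold on baseline. A slope between 0 and 1 reduces the bias but does not remove it.

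**Step 4: illustration.** None of these inputs is in the documents. Slope is taken as 0.6-0.8.

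| Case | Share × days × dB/day | Shift (dB) | Adjusted bias (dB) |
|---|---|---|---|
| Low | 0.2 × 4 × 0.5 | 0.4 | 0.24-0.32 |
| Middle | 0.3 × 5 × 0.9 | 1.35 | 0.81-1.08 |
| High | 0.5 × 7 × 1.2 | 4.2 | 2.52-3.36 |

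The middle rate is half the planned 25 dB gain over two weeks: 12.5/14 = 0.89 dB/day. That gain is for treated control participants, so it probably overstates untreated recovery. A much slower course, 32% of 25 dB = 8 dB spread evenly over 84 days, is 0.095 dB/day. The middle case then becomes 0.3 × 5 × 0.095 = 0.14 dB, or 0.09-0.11 dB adjusted. The answer moves about tenfold on this one assumption.

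**Step 5: what a given net bias would cost.** SE = 25 × √(2/157) = 2.82 dB; critical value 2.241. Rejection probability = Φ(m/SE − 2.241) + Φ(−m/SE − 2.241), with m = 10 − b for a true 10 dB intratympanic benefit and m = −b for no difference.

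| Net bias b (dB) | Power for true +10 dB | Rejection with no difference |
|---|---|---|
| 0 | 90% | 2.5% |
| 0.3 | 88% | 2.6% |
| 1 | 83% | 3.4% |
| 3 | 60% | 12.0% |

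These keep the SD at 25 dB; the gain in precision from baseline adjustment is ignored.

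**The case against.** A reader might infer that recovery *is* removed from the intratympanic-only arm and that its comparison with oral treatment *is* biased. The documents do not support that.

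- **Same visit.** Section 9 and Table 3 put oral provision and the first injection at the same Baseline visit, and the same-or-next-working-day aim applies to every arm. Followed as written, one audiogram serves everyone and the bias is zero.
- **Not arm-specific.** A late oral start would trigger the same rule. The four-day tolerance in the combined arm runs in both directions and says nothing direct about the intratympanic-only arm.
- **No ordered repeat.** Section 7.3 plans pre-injection audiograms before the second and third injections only. Section 11.2 keeps the first result when a test is repeated for confirmation.
- **Table 9.** Its entry, "At baseline (i.e. following consent and randomisation", stands in the submission-schedule column. It says when the form is due, not when hearing was tested. Audiometry is transcribed from clinical notes (Table 8), so the form can carry the earlier result.

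All of this stands against a claim of certain bias. It does not settle which audiogram is the baseline. A repeat made because the window lapsed is not clearly confirmatory, so sites may differ. A statistical analysis plan, not at hand, could name the earlier value, but the protocol fixes when sites must test.

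**Conclusion.** The point holds as a conditional weakness in the outcome definition. The baseline is tied to a post-allocation event, the end point is tied to randomisation, the time between randomisation and treatment has no stated limit, and the pre-randomisation audiogram is not named as the baseline. A bias follows only if starts more than 3 days after that audiogram are more common in one arm and the repeat replaces the earlier value. If the later arm were intratympanic-only, the direction would be against intratympanic treatment.

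The size cannot be derived, because the protocol gives neither delay by arm nor the time course of spontaneous recovery. The illustration runs from zero, through about 1 dB in the middle case, to 3.4 dB at an extreme where every assumption is unfavourable. It shows what is possible and is not an estimate. This is a cheap improvement worth making, not evidence that the planned comparison is invalid.

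**What to change.** In sections 8.2.1 and 9 and in Table 3:

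1. Define the primary-outcome baseline, in all three arms, as the last pure tone audiogram before randomisation, the one that supplies the minimisation severity stratum.
2. Count its 3-day window back from randomisation.
3. Record any audiogram repeated after randomisation and before first treatment, but do not let it replace the baseline.
4. Report time from randomisation to first treatment by arm.

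This changes the outcome definition only and sets no treatment timing. The cost is protocol and case report form wording. It adds no test: an audiogram more than 3 days old at randomisation is also more than 3 days old at treatment start, so the present rule would already call for a new one. The small downside is that the baseline will be a few days older at first treatment in participants with a delayed start.
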